### Randomization and Blinding

Randomization sequences were generated prior to study initiation by an independent statistician using the R software (R Foundation for Statistical Computing). Participants were stratified by PrEP dosing regimen (daily vs event driven) based on their self-report. Within each stratum, participants were randomized in a 1:1 ratio to the intervention or control group using variable block randomization with randomly permuted block sizes of 4 and 6. As a result, each group will have 215 participants, with 160 event-driven users and 55 daily users (Figure 1). The study adopted an open-label design because the nature of the intervention makes blinding infeasible.

**Figure 1 figure1:**
[figure not shown]
Flowchart of recruitment and follow-up procedures of the study. PrEP: preexposure prophylaxis.

### Control and Intervention Description

#### Real-Time Monitoring

All the participants in both the control and intervention groups will be invited to use a WeChat-based digital platform named PLP Camp (Figure 2). PLP Camp allows participants to electronically record their PrEP adherence and related sexual behaviors in a timely manner based on the EMA principles of interval- and event-contingent recording. Daily users will receive an SMS text message every 24 hours at a self-predetermined time (interval contingent) to remind them to log on to the platform and record whether they have taken their daily pill in the previous 24 hours. Event-driven users are asked to actively log on to the platform and record their PrEP-taking behavior for each sexual encounter (event contingent). In addition, they will receive an SMS text message every 72 hours at a self-predetermined time (interval contingent) to remind them to log on and record their PrEP-taking behaviors in the previous 72 hours.

**Figure 2 figure2:**
[figure not shown]
PLP Camp screenshots of the adherence recording journey from the user end.

According to the records of PrEP-taking and related sexual behaviors, the platform will automatically calculate each participant’s risk level of nonadherence (ie, high, medium, or low risk). The criteria for risk classification are shown in Table 1. The risk level will be assessed every 3 days, with a comprehensive risk assessment report sent to the participants on a weekly basis. Participants who do not report any adherence during each risk assessment period will continue to be assigned their last reported risk level. Moreover, those who are inactive more than 3 times will be kindly reminded to log into the platform via WeChat. The detailed stratification is shown in Table 1. The PLP Camp platform used by the control group (simple version) will only include the function of real-time monitoring with risk assessment.

**Table 1 table1:** Criteria for risk classification of preexposure prophylaxis (PrEP) nonadherence in the Real-Time Monitoring and Precision Intervention for HIV PrEP Adherence trial.

Regimen and risk level			Risk assessment criteria
**Event-driven PrEP**			
	Low risk	Correct medication taken for every sexual encounter	
	Medium risk	Medication taken for every sexual encounter but with partial correct use (ie, incorrect use for at least 1 of the 2-1-1 time points) sometimes or medication not taken for every encounter but with correct use whenever taken	
	High risk	Medication not taken for every sexual encounter and instances of incorrect use	

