#### Precision Intervention Component

The full version of the PLP Camp platform used by the intervention group will additionally incorporate precision intervention functions. On the basis of the results of the risk assessment, participants at different risk levels will receive precise and targeted interventions [26]. The intervention is designed based on the assumption that different risk levels of PrEP nonadherence correspond to different stages of change toward optimal adherence, as shown in Figure 3. It is assumed that high risk means that the participants are not ready to adhere to PrEP at all or they are just starting to think about adhering, medium risk means that the participants are starting to think about adhering and preparing to adhere to PrEP, and low risk means that they are currently practicing and maintaining optimal adherence. The intervention was developed through a multistage, theory-informed, and user-centered process. It was grounded in the SCT and TTM, which conceptualize adherence as a gradual behavioral progression. Guided by this framework, we mapped levels of nonadherence risk to corresponding stages of change, thereby enabling delivery of tailored intervention components according to participants’ behavioral readiness [27]. This theoretical alignment ensured that participants with lower readiness received more intensive behavioral support, whereas those with higher readiness received informational and reinforcement support. Different behavior change techniques are used for different risk levels. Each intervention component was aligned with TTM constructs [27].

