**Figure 3 figure3:**
[figure not shown]
Conceptual framework of the precision intervention. AI: artificial intelligence; PrEP: preexposure prophylaxis.

Low-risk participants accessed weekly health education (eg, HIV and PrEP knowledge, importance and benefits of good adherence, and ways to keep mentally well) and an artificial intelligence (AI) chatbot for counseling (eg, answering questions about correct instructions for PrEP), corresponding to the action and maintenance stages. These modules operationalized counterconditioning by helping participants replace unhelpful behaviors and beliefs with health-promoting alternatives. The AI chatbot provided timely responses to basic questions about PrEP and HIV, reducing anxiety and encouraging proactive problem-solving, whereas the weekly health education delivered evidence-based content and positive narratives that fostered mindfulness, self-efficacy, and constructive attitudes toward adherence.

Medium-risk participants accessed an interactive forum and admonitory education (eg, exemplars and narratives about HIV infection due to PrEP nonadherence), corresponding to the contemplation and preparation stages. The interactive forum mapped to helping relationships, enabling peer exchange and collective problem-solving. The admonitory education module aligned with stimulus control, guiding participants to recognize triggers—such as social situations, travel, or stress—and restructure their environment to support adherence.

High-risk participants received personalized medication reminders (tailored pop-up messages) and expert consultation (web seminars and online individual sessions), corresponding to the precontemplation and contemplation stages. The reminder system reflected consciousness raising by promoting self-observation and awareness of missed doses, whereas the expert consultation module embodied emotional arousal (dramatic relief) by helping participants express emotions related to adherence and receive encouragement and hope through empathetic guidance.

Examples of the platform modules are shown in Figure 4. As the risk level of each participant may change throughout the study period, the intervention modules will be automatically adjusted by the platform based on the participant’s weekly adherence report.

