**Figure 4 figure4:**
[figure not shown]
PLP Camp screenshots of each intervention module from the user end. AI: artificial intelligence.

Intervention delivery will be implemented through the PLP Camp platform, with all modules and the check-in function accessible via participants’ mobile devices. Participants will log into PLP Camp through WeChat, ensuring seamless integration with a widely used app. Health education materials are available on the home page and presented in chronological order according to publication time. To promote outreach, the research team will also send health education materials to participants one-to-one via WeChat. The AI chatbot is also accessible from the home page; selecting this feature directs users to an interactive dialogue interface. Admonitory education is provided within the health education section under a dedicated subtab titled “Their Story.” The peer forum is accessible via the “Forum” button on the settings page, where participants can create posts, comment, and engage with others through likes. Personalized medication reminders are automatically triggered when participants are first classified as high risk and can subsequently be accessed through the settings page. Additionally, the “Consult Expert” function, located on the settings page, connects participants to a professional PrEP consultant through a real-time dialogue interface.

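### As worded, Table 1's event-driven high-risk row excludes users who report sex but take no PrEP; the daily row also glosses 80% as 25 of 30 days when 24 of 30 is 80%

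*Protocol article*

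**What the plan says.** Table 1 (Methods, Real-Time Monitoring) sets the tiers of nonadherence risk.

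- **Event-driven, low:** correct dosing at every encounter.
- **Event-driven, medium:** either PrEP at every encounter but *sometimes* wrong at one or more 2-1-1 time points, or "medication not taken for every encounter but with correct use whenever taken".
- **Event-driven, high:** "Medication not taken for every sexual encounter and instances of incorrect use".
- **Daily:** low is 80% or more, explained as 25 days or more in 30; medium is 40% to 80%, explained as 12 to 24 days; high is below 40%, fewer than 12 days.

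On timing, "The risk level will be assessed every 3 days". The Precision Intervention Component section gives the intended meaning: "high risk means that the participants are not ready to adhere to PrEP at all or they are just starting to think about adhering". It adds that people with lower readiness get more intensive support. On content, "High-risk participants received personalized medication reminders (tailored pop-up messages) and expert consultation", and "Personalized medication reminders are automatically triggered when participants are first classified as high risk".

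**The concern.** The high-risk row joins a missed encounter and incorrect use with *and*. Elsewhere in the table, incorrect use means an error at a 2-1-1 time point, and correct use is judged only when PrEP was taken. Someone who takes nothing has no course that could be incorrect, so the least adherent user falls outside the tier meant for the least ready.

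The tier decides which tailored content an intervention-arm participant receives, and that content is the only planned difference between the arms. A literal implementation would withhold the personalized reminders from complete non-users. Even if the code does something else, readers cannot tell from the article what was delivered to these users.

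**Working it through.** **Inputs.** The rows of Table 1; the meaning of high risk and the intensity gradient (Precision Intervention Component); the daily cut-off of 80% or higher for optimal adherence (Outcomes).

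**1. Event-driven rows applied literally.** Code each reported encounter as C (taken correctly), I (taken incorrectly) or N (not taken). All patterns for two encounters:

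| Pattern | Tier as worded |
|---|---|
| C, C | low |
| C, I | medium, first clause |
| I, I | medium only if *sometimes* includes always; otherwise no row |
| C, N | medium, second clause |
| I, N | high |
| N, N | medium only vacuously; otherwise no row |

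With one encounter, C is low, I behaves as I, I, and N behaves as N, N. A one-encounter record can never be high risk.

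For n encounters there are (n+1)(n+2)/2 patterns; for n = 10 that is 11 × 12 / 2 = 66.

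- Low: 1 (all C).
- Medium, first clause: 9 mixtures of C and I with no N, plus all-I if *sometimes* includes always.
- Medium, second clause: 9 mixtures of C and N with no I.
- High (at least one I and one N): 9 + 8 + ... + 1 = 45.
- All-N: 1, with no row unless the second medium clause is met vacuously.

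The total is 1 + 10 + 9 + 45 + 1 = 66. One pattern lacks a clear row if *sometimes* is read generously, and two if it is read as strictly as the high-risk row. These are counts of patterns, not of people.

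**2. The inversion.** Of 10 encounters, 8 C, 1 I and 1 N meets the high-risk row; 10 N does not. The Precision Intervention Component section implies the opposite order for the second user.

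**3. Readings that might rescue the row.**

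- *Non-use counts as incorrect use.* Every missed encounter is then high risk, and the second medium clause has no one left to describe.
- *Not taken for every encounter means not taken for any.* Incorrect use is still required and then cannot occur.
- *Carry-forward:* "Participants who do not report any adherence during each risk assessment period will continue to be assigned their last reported risk level". The next sentence concerns inactive participants, so this is best read as covering people who submit no report. Even read more widely, it only leaves the user at the last tier.
- *High is whatever remains.* The table does not say so; it gives high risk its own criterion.

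**4. Daily rows.** The plan's figure: 25/30 = 83.3%. The smallest d with d/30 ≥ 0.80 is 0.80 × 30 = 24, and 24/30 = 80.0% exactly. Twenty-five days follows only from a strict >80% rule (24/30 fails) or a 31-day period (0.80 × 31 = 24.8, rounded up to 25). At 24 of 30 a user is low by percentage, medium by day count, and at the level the Outcomes section calls optimal. The percentage bands also both contain 80%. The lower cut is right: 12/30 = 40.0% and 11/30 = 36.7%.

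Exactly 80% needs a window whose length is a multiple of 5. It cannot occur over 3 days (2/3 = 66.7%, then 100%) or 7 days (5/7 = 71.4%, 6/7 = 85.7%), but it can over 30.

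**The case against.** The strongest reply is that this is condensed table wording. The platform calculates the tier automatically, its code is not shown, and it may well place non-users in high risk. Order of precedence and look-back window are details that an article may leave to a fuller specification. This stands as far as consequences go: no misrouting has been shown. It does not remove the point, because the criterion is stated rather than omitted, and it gives the wrong tier if followed.

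The loss is also limited. Both arms receive check-in messages, and a non-user placed in medium still gets the forum and admonitory education. Expert consultation is listed for high risk, but the article also says that this "function, located on the settings page, connects participants to a professional PrEP consultant through a real-time dialogue interface", with no stated tier limit. So a reader might infer that non-users lose expert consultation too, but the text does not settle that. Only the personalized reminder is clearly tied to high risk.

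A reader might also infer that the primary result is biased by the table. It is not: the Outcomes section classifies adherence by its own rules. Nor are the 160 planned event-driven intervention-arm users (160/215 = 74%) the number affected; they are everyone the rule governs.

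Finally, the daily slip is close to editorial. It touches only users at exactly 80%, and code that tests for 80% or more first would misroute nobody. Nothing requires the routing and outcome cut-offs to be identical. Even so, the percentage and the day count in one row should agree.

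**Conclusion.** The point holds as a defect in the stated rule. As worded, an event-driven user who reports encounters and takes no PrEP cannot be high risk and is medium only vacuously, contrary to the stated meaning of high risk. Under an equally strict reading, a user who always takes PrEP but always incorrectly has no row either. The daily mismatch at 24 of 30 days is real but minor.

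The practical size cannot be determined, because neither the platform code nor the share of complete non-users is given. The conclusion about withheld reminders is conditional on literal coding. No effect on the primary outcome definition is claimed.

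**What to change.** Event-driven rows:

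- **High:** add *or medication not taken for any reported encounter*.
- **Medium, second clause:** limit it to users with at least one correctly taken course.
- **Medium, first clause:** replace *sometimes* with *at least once*.

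Every pattern then has exactly one tier. For n = 10: low 1, medium 10 + 9 = 19, high 45 + 1 = 46, total 66.

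Daily rows: low ≥80% (24 days or more of 30); medium 40% to <80% (12 to 23 days); high <40% (fewer than 12 days).

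Then check the live code against the corrected table, correct it if it follows the literal wording, and report which rule was delivered and when.

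The cost is a table correction and a code check. The intervention is described as running until August 2026, so any change during follow-up should be dated.

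The fix closes the unassigned patterns only. A user with 1 correct and 9 missed encounters stays medium while 8 correct, 1 incorrect and 1 missed stays high, and a single reported, missed encounter becomes high risk. Whether to re-rank partial non-users is a design choice for the investigators.

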**Daily PrEP**			
	Low risk	≥80% medication adherence (ie, taking medication on at least 25 out of 30 d)	
	Medium risk	40%-80% medication adherence (ie, taking medication on 12-24 out of 30 d)	
	High risk	<40% medication adherence (ie, taking medication on less than 12 d in a 30-d period)	

#### Precision Intervention Component

The full version of the PLP Camp platform used by the intervention group will additionally incorporate precision intervention functions. On the basis of the results of the risk assessment, participants at different risk levels will receive precise and targeted interventions [26]. The intervention is designed based on the assumption that different risk levels of PrEP nonadherence correspond to different stages of change toward optimal adherence, as shown in Figure 3. It is assumed that high risk means that the participants are not ready to adhere to PrEP at all or they are just starting to think about adhering, medium risk means that the participants are starting to think about adhering and preparing to adhere to PrEP, and low risk means that they are currently practicing and maintaining optimal adherence. The intervention was developed through a multistage, theory-informed, and user-centered process. It was grounded in the SCT and TTM, which conceptualize adherence as a gradual behavioral progression. Guided by this framework, we mapped levels of nonadherence risk to corresponding stages of change, thereby enabling delivery of tailored intervention components according to participants’ behavioral readiness [27]. This theoretical alignment ensured that participants with lower readiness received more intensive behavioral support, whereas those with higher readiness received informational and reinforcement support. Different behavior change techniques are used for different risk levels. Each intervention component was aligned with TTM constructs [27].

**Figure 3 figure3:**
[figure not shown]
Conceptual framework of the precision intervention. AI: artificial intelligence; PrEP: preexposure prophylaxis.

Low-risk participants accessed weekly health education (eg, HIV and PrEP knowledge, importance and benefits of good adherence, and ways to keep mentally well) and an artificial intelligence (AI) chatbot for counseling (eg, answering questions about correct instructions for PrEP), corresponding to the action and maintenance stages. These modules operationalized counterconditioning by helping participants replace unhelpful behaviors and beliefs with health-promoting alternatives. The AI chatbot provided timely responses to basic questions about PrEP and HIV, reducing anxiety and encouraging proactive problem-solving, whereas the weekly health education delivered evidence-based content and positive narratives that fostered mindfulness, self-efficacy, and constructive attitudes toward adherence.

Medium-risk participants accessed an interactive forum and admonitory education (eg, exemplars and narratives about HIV infection due to PrEP nonadherence), corresponding to the contemplation and preparation stages. The interactive forum mapped to helping relationships, enabling peer exchange and collective problem-solving. The admonitory education module aligned with stimulus control, guiding participants to recognize triggers—such as social situations, travel, or stress—and restructure their environment to support adherence.

High-risk participants received personalized medication reminders (tailored pop-up messages) and expert consultation (web seminars and online individual sessions), corresponding to the precontemplation and contemplation stages. The reminder system reflected consciousness raising by promoting self-observation and awareness of missed doses, whereas the expert consultation module embodied emotional arousal (dramatic relief) by helping participants express emotions related to adherence and receive encouragement and hope through empathetic guidance.

Examples of the platform modules are shown in Figure 4. As the risk level of each participant may change throughout the study period, the intervention modules will be automatically adjusted by the platform based on the participant’s weekly adherence report.

**Figure 4 figure4:**
[figure not shown]
PLP Camp screenshots of each intervention module from the user end. AI: artificial intelligence.

Intervention delivery will be implemented through the PLP Camp platform, with all modules and the check-in function accessible via participants’ mobile devices. Participants will log into PLP Camp through WeChat, ensuring seamless integration with a widely used app. Health education materials are available on the home page and presented in chronological order according to publication time. To promote outreach, the research team will also send health education materials to participants one-to-one via WeChat. The AI chatbot is also accessible from the home page; selecting this feature directs users to an interactive dialogue interface. Admonitory education is provided within the health education section under a dedicated subtab titled “Their Story.” The peer forum is accessible via the “Forum” button on the settings page, where participants can create posts, comment, and engage with others through likes. Personalized medication reminders are automatically triggered when participants are first classified as high risk and can subsequently be accessed through the settings page. Additionally, the “Consult Expert” function, located on the settings page, connects participants to a professional PrEP consultant through a real-time dialogue interface.

### Data Collection

Data for the REMOTE trial will be collected in 2 ways: from the PLP Camp platform and from the baseline and follow-up surveys. The real-time monitoring function of PLP Camp is able to record participants’ PrEP adherence behaviors and related sexual behaviors. The baseline and 1-, 3-, and 6-month follow-up surveys will be self-administered via an electronic questionnaire. Data will be collected by 2 trained research staff members. Sociodemographic information, current PrEP regimen, sexual behaviors, PrEP adherence, PrEP knowledge and perceptions, facilitators of and barriers to PrEP adherence, PrEP stigma and self-efficacy, social support, and other psychosocial variables will be collected (S1, baseline questionnaire; Multimedia Appendix 1). PrEP adherence will be measured by asking participants whether they took PrEP for each sexual encounter and whether they took it strictly as instructed. A PrEP knowledge question will be extracted from the guidelines for taking PrEP [28]. PrEP stigma will be measured using an HIV PrEP stigma scale [29]. PrEP self-efficacy will be measured using an adapted version of the Condom Use Self-Efficacy Scale [30]. Psychosocial variables will be measured using the Patient Health Questionnaire–9, the 2-item Connor-Davidson Resilience Scale, and the 7-item Generalized Anxiety Disorder Scale [31-33]. Follow-up questionnaires will include the same variables, with extra measures of the feasibility and acceptability of the intervention. Feasibility and acceptability will be measured using the Feasibility of Intervention Measure and Acceptability of Intervention Measure scales combined with PLP Camp use and the Intervention Appropriateness Measure scale (S2; Multimedia Appendix 2) [34]. The link to access the questionnaires will be sent to the participants via WeChat, and each survey will take an average of no more than 10 minutes to complete.

